**Trial Registration:**

ClinicalTrials.gov NCT06304207; https://clinicaltrials.gov/study/NCT06304207

**International Registered Report Identifier (IRRID):**

DERR1-10.2196/71039

## Introduction

Chronic lung disease (CLD), an umbrella term for persistent lung conditions, including chronic obstructive pulmonary disease (COPD), interstitial lung disease, bronchiectasis, and chronic asthma, is a major contributor to the global burden of disease [1,2]. Patients with CLD are often trapped in the downward spiral of mobility, where symptoms such as dyspnea and fatigue limit physical activity [3,4]. Reduced activity levels further accelerate disease progression, leading to declines in muscle strength, deconditioning, and worsening of symptoms [3,4]. Consequently, patients experience increased respiratory exacerbations, resulting in frequent hospitalizations and readmissions, impacting the quality of life and health care costs [5-9].

Pulmonary rehabilitation (PR) has been reported as one of the most evidence-based, cost-effective, and efficient interventions to improve health outcomes in CLD [5-9]. The American Thoracic Society/European Respiratory Society statement defines PR as “a comprehensive intervention based on a thorough patient assessment followed by patient-tailored therapies, which include, but are not limited to, exercise training, education, and behavior change, designed to improve the physical and emotional condition of people with chronic respiratory disease and to promote the long-term adherence of health-enhancing behaviors” [5]. Compared to medical management alone, strong evidence supports PR to improve lung function, exercise capacity, physical function, self-efficacy, quality of life, and physical activity while also delaying disease progression and reducing the risk of hospitalization and mortality [5-9].

Despite strong evidence demonstrating PR effectiveness, reported benefits rapidly decline after discharge in the absence of supervised maintenance as adherence to health-enhancing behaviors and physical activity levels wane over time [10,11]. To promote long-term adherence, patients may need a continuum of care with tapered supervision beyond formal PR. Supervised maintenance programs involve ongoing supervised exercise at a lower frequency than PR programs. Although an abundance of literature supports the benefits of PR, studies examining maintenance programs are scarce and demonstrate mixed results. Limited studies using community-based supervised maintenance following PR have demonstrated a strong potential of these programs in maintaining a variety of outcomes, including physical activity level, quality of life, 6-minute walk distance, and dyspnea scores [12], but other studies on maintenance have failed to demonstrate these benefits [13,14]. Overall, the certainty of evidence on the benefits of maintenance programs is deemed low, particularly due to inconsistent performance on outcome measures, high risk of bias, lack of rigorous methodologies, attrition, and small sample sizes [15]. Ongoing improvements in outcomes are believed to result from enhanced function, exercise tolerance, and symptom control with structured maintenance programs [6,7,15]. However, access barriers and adherence challenges persist, highlighting the need for feasible, scalable models like telehealth [16]. These limitations underscore the need for well-designed studies to evaluate the feasibility and effectiveness of supervised maintenance programs, particularly those delivered via telehealth.

One method to improve adherence in maintenance programs is telerehabilitation (tele-rehab), which is a way of participating in medical appointments via a technology device [17]. Tele-rehab is a viable alternative rehabilitation approach for patients with CLD and holds potential as an effective tool for increasing positive behavioral changes, including long-term adherence and a more physically active lifestyle [18-21]. Few studies [18,22-24] have compared the benefits of tele-rehab versus onsite PR on health outcomes in people living with CLD, and even fewer studies have compared supervised maintenance programs delivered via tele-rehab with onsite maintenance, leaving many gaps in the literature [25]. Furthermore, most studies are limited to people with COPD, with only a small number investigating the effects of tele-rehab on other CLDs [26,27].

Given these limitations, there is a clear need for well-designed feasibility studies to evaluate the effectiveness and practicality of supervised maintenance programs, particularly those delivered via telehealth. The purpose of this pilot feasibility trial is to (1) assess the feasibility of delivering an 8-week supervised maintenance program remotely via tele-rehab in comparison to onsite delivery and (2) compare the effectiveness of these interventions on clinical outcomes in patients with CLD. We hypothesize that tele-rehab will be feasible to implement, with acceptable adherence, and will yield comparable improvements in clinical outcomes to onsite rehabilitation.

## Methods

### Ethical Considerations

The study protocol has been reviewed and approved by the institutional review board at Massachusetts Brigham (approval 2023P000708). The study protocol is registered on Clinicaltrials.gov (NCT06304207). Any changes to the protocol will be reported to the institutional review board by the principal investigator. Participants will provide verbal consent during a phone call after being prescreened for eligibility. A signed consent form will then be obtained either in person during their baseline assessment or electronically through Research Electronic Data Capture (REDCap) [28]. Institutional affiliations (eg, Massachusetts Brigham and the MGH Institute of Health Professions) will be transparently presented to the participants during recruitment to ensure trust and informed decision-making. In order to protect the participant's privacy, all recorded data will be deidentified and stored in a password-protected computer. This information will then be destroyed at the end of the study. All study team members underwent training on protecting data privacy. To reduce the barriers to participation and to encourage enrollment, we will provide free parking for onsite visits; an iPad will be loaned for the study duration if needed for tele-rehab, and a US $50 gift card will be provided upon study completion.

### Study Design

This study follows the CONSORT (Consolidated Standards of Reporting Trials; Multimedia Appendix 1) and SPIRIT (Standard Protocol Items: Recommendations for Interventional Trials; Multimedia Appendix 2) guidelines. The study will be a randomized, assessor-blinded, pilot feasibility trial. Participants will be randomly assigned in a 1:1 allocation ratio to either (1) a tele-rehab group with remotely supervised intervention or (2) an onsite group with in-person supervision. Figure 1 outlines the study design and recruitment process. The anticipated study period is from September 1, 2023, to April 1, 2026.

**Figure 1 figure1:**
[figure not shown]
Participant Recruitment and Allocation.

Given the higher prevalence of CLD in late adulthood [29-31], individuals aged 40 years and older with a physician-confirmed diagnosis of CLD will be recruited for this study. Inclusion criteria include the ability to understand English instructions, walk independently with or without the use of mobility devices, complete a 6-minute walk test (6MWT) while maintaining oxygen saturation of at least 85% with or without supplemental oxygen, a history of onsite rehabilitation completion, and internet access, which will be verified by accessing email for communication. Exclusion criteria include medical conditions causing significant mobility limitations such as stroke, Parkinson disease, multiple sclerosis, or severe degenerative joint disease. Participants will also be excluded if they are unable to maintain oxygen saturation of at least 85% during 6MWT, have baseline hemodynamic instability (eg, unstable angina, recent myocardial infarction within 3 months, uncontrolled atrial fibrillation), advanced heart failure (New York Heart Association Class IV), or require mechanical circulatory support such as ventricular assist devices.

### Participant Enrollment

Eligible participants will be recruited through clinical settings, offline outreach, and direct contact by study team members. During recruitment, participants will receive detailed verbal information about the study, including the randomization process, assessments, and intervention details.

### Study Procedures

#### Onsite Initial Evaluation

After providing informed consent, all participants will complete a baseline assessment at [name] and Ann Saunders IMPACT Practice Center at MGH Institute of Health Professions. This initial visit, conducted by an assessor blinded to group allocation, will serve as the index date, referred to as time point 0 (time0). Since recruitment will occur on a rolling basis, time0 will vary for each participant. During the baseline visit, the assessor will review the self-monitoring of vitals and symptom provocation with participants. Education on monitoring oxygen saturation by using pulse oximetry, rate of perceived exertion, and heart rate will be provided in detail. Additionally, participants will receive a pulse oximeter and a Threshold Inspiratory Muscle Trainer Respironics positive expiratory pressure device during the baseline visit to use throughout the study.

#### Random Assignment

Following the baseline assessment, a separate research team member will contact each participant via phone to communicate the randomized group assignment. Participants will be randomly assigned to one of the 2 groups: (1) tele-rehab, where the participants receive supervised intervention remotely at home or (2) onsite outpatient rehabilitation. A web-based randomization service [32] will be used to generate random assignments to eliminate allocation bias.

#### Outcome Assessments

Outcomes will be recorded in-person at 3 time points: at baseline before the intervention (time0), at the end of the 8-week intervention (time1), and at 1-month post intervention during follow-up (time2). A blinded study team member will conduct all outcome assessments at each time point (Table 1), with reminder emails sent to participants during the week the assessment is scheduled. Feasibility outcomes will include the number of sessions attended post randomization, the ease of using equipment and procedures, optimal session length, and adherence as measured by the daily activity log. Clinical outcomes will include baseline vitals such as heart rate, respiratory rate, oxygen saturation measured with a pulse oximeter, Borg rating of perceived exertion [33], and modified Medical Research Council dyspnea scale [34,35]. Respiratory muscle strength will be evaluated using maximal inspiratory pressure, while physical function will be assessed with the 30-second chair rise test [36] and the 10-meter walk test [37]. Functional capacity will be measured through 6MWT [38,39] and the 10-meter incremental shuttle walk test [40]. Physical activity will be assessed using the International Physical Activity Questionnaire [41], and the quality of life will be evaluated with the Patient-Reported Outcomes Measurement Information System Global Health Questionnaire [42] and the COPD Assessment Test [43]. Secondary outcomes will include planned or unplanned physician visits, emergency room visits, falls, and injuries.

**Table 1 table1:** Interventions provided for tele-rehab^a^ and onsite rehab^b^ groups.

Goal (duration)	Tele-rehab group and onsite rehab group
Check-in and education (5 min)	Review of activities during the week at home Symptom changes during the week Education on self-management of airway clearance Education on the importance of maintaining regular physical activity
Breathing retraining (5 min)	Inspiratory muscle training using a Threshold Inspiratory Muscle Trainer at 30%-50% of maximal inspiratory pressure
Warm-up (5 min)	Spot marching Stretching large group muscles
Aerobic exercise (25 min)	Treadmill/cycle ergometer/NuStep/walking/stair climbing^c^ Treadmill walking: initial walking speed at 60%-85% of peak VO2^d^ estimated from 6MWT^e^ and/or rate of perceived exertion of 13-16 (somewhat hard to hard) corresponding to 60%-85% of peak VO2 Cycle ergometer and NuStep intensity at rate of perceived exertion of 13-16 or a resistance corresponding to 60%-85% of peak VO2 derived from published equations Overground walking or stairs at rate of perceived exertion of 13-16 (somewhat hard to hard) corresponding to 60%-85% of peak VO2
Functional strengthening (15 min)	Partial squats, sit-to-stand exercise, lunges, and step-ups/downs 3 sets of 10 repetitions each
Cool down (5 min)	Spot marching Stretching of large group muscles

^a^Tele-rehab: telerehabilitation group. This group receives remotely supervised sessions conducted via videoconferencing.

^b^Onsite-rehab: onsite maintenance rehabilitation. This group receives onsite maintenance rehabilitation with in-person sessions.

^c^No stair climbing in the onsite rehabilitation group.

^d^VO_2_: oxygen consumption.

^e^6MWT: 6-minute walk test.

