**Methods:**

This randomized, assessor-blinded feasibility pilot trial will enroll 30 participants who have completed outpatient PR. Participants will be randomized into 2 groups: (1) tele-rehab, involving remotely supervised sessions conducted via videoconferencing or (2) onsite maintenance rehabilitation with in-person sessions. Both groups will receive weekly supervised sessions for 8 weeks facilitated by licensed physical therapists. Assessments will be conducted onsite at baseline, after the 8-week intervention, and at 1-month follow-up by a blinded assessor. The feasibility of the intervention and the study methods will be assessed by the log-in into the number of sessions attended after randomization, the ease of using the equipment and procedures, optimal session length, and adherence to the intervention protocol. Clinical outcomes will include dyspnea and perceived exertion, respiratory muscle strength, physical function, 6-minute walk distance, physical activity, and quality of life. Descriptive statistics with means and standard deviations for continuous and frequency distributions for categorical data will be utilized to report individual and group characteristics. Feasibility outcomes will be compared using independent 2-sided *t* tests. Between-group comparisons will use mixed analysis of variance, and within-group comparisons will be analyzed with a repeated measures analysis of variance.

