### Statistical Analysis

Since a large 2-group comparative study has not yet been published, this pilot study will generate an estimate of variance and the percentage of change in outcomes needed to determine the power and sample size for a larger study. Therefore, estimation rather than statistical testing is the main objective of this study. Given the possibility of attrition from dropouts, we will recruit 40 participants with a goal to have 30 participants complete the study (15 in each group). Descriptive statistics will be used to summarize the demographic and clinical characteristics and outcomes for all the participants. Feasibility will be assessed using frequency distributions of session adherence and use of activity logs. Comparisons between groups on all outcomes at preintervention and postintervention will be conducted with the intention to treat using a mixed analysis of variance. Within-group comparisons at all 3 time points will be conducted via a repeated measures analysis of variance. Adherence to the program between groups will be compared using independent 2-sided *t* tests. Finally, descriptive statistics with frequency distributions of adverse events, planned and unplanned physician visits, and frequency of use of daily activity log will be reported.

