### Limitations

There are several limitations that we would like to acknowledge. Although we anticipate achieving a feasible, acceptable, and high-fidelity protocol, it is possible that some challenges remain. Given a feasibility pilot, we anticipate being underpowered to assess intervention efficacy. Despite the randomized design, allocation concealment is not possible. The risk of participants dropping out after learning their allocation assignment cannot be ruled out. We have taken measures to minimize this risk by having trained research staff instead of staff manage action planning and SMS text messaging procedures to avoid any accidental information exchange about other participants. Although steps are taken to improve access to all potential individuals, limiting inclusion to participants who speak English may limit the reach to participants who have limited English proficiency.

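### The patient-reported questionnaires are tied to onsite visits with no remote route described, so a missed time1 or time2 visit also loses that time point's questionnaire data

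*Protocol article*

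**What the plan says.** Collection mode is stated, not left open. Outcome Assessments says "Outcomes will be recorded in-person at 3 time points", meaning baseline (time0), the end of the 8-week program (time1) and one month later (time2). The same section adds that "A blinded study team member will conduct all outcome assessments at each time point". The Methods paragraph of the Abstract agrees: "Assessments will be conducted onsite at baseline, after the 8-week intervention, and at 1-month follow-up by a blinded assessor".

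The outcomes listed under that rule are of two kinds.

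- **Measured at the site:** vital signs, maximal inspiratory pressure, the chair-rise, 10-meter walk, 6-minute walk and shuttle walk tests.
- **Reported by the patient:** the mMRC dyspnea scale, physical activity ("Physical activity will be assessed using the International Physical Activity Questionnaire") and quality of life ("the quality of life will be evaluated with the Patient-Reported Outcomes Measurement Information System Global Health Questionnaire", together with the CAT).

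No route is described for obtaining the second kind from someone who does not attend.

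Other data do not depend on the assessment visits. Under Onsite Group, attendance is recorded at each session, and participants keep a daily log and report physician and emergency visits, falls and injuries. Tele-Rehab Group adopts the same protocol.

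On retention, Statistical Analysis says "Given the possibility of attrition from dropouts, we will recruit 40 participants with a goal to have 30 participants complete the study", declares intention to treat, and makes estimation the main objective. Limitations concedes that "The risk of participants dropping out after learning their allocation assignment cannot be ruled out". REDCap appears under Ethical Considerations, where signed consent may be obtained "electronically through Research Electronic Data Capture (REDCap").

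**The concern.** Standardized conditions are a good reason to run walk tests and inspiratory pressure at the site. That reason does not extend to questions about breathlessness, activity and quality of life. As written, someone who cannot travel in week 8 but would answer a questionnaire contributes nothing at that time point.

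Three features make this matter here.

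- Estimation is the main objective, so lost precision bears directly on the trial's purpose.
- The analyses named are a mixed ANOVA (before and after the intervention) and a repeated measures ANOVA (three time points). In their conventional form both use complete cases. Unless missing values are handled in some other way, one missed visit removes the participant from the three-time-point analysis of that outcome.
- The trial's rationale, set out in the Discussion, is that people struggle to reach a site. Its follow-up of patient-reported outcomes depends on their reaching one.

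**Working it through.** **Inputs.** From Statistical Analysis: 40 recruited, 30 completing, 15 per group. From Study Design: 1:1 allocation, so 20 per group at randomization. The article gives no dropout rate, SD or share of non-completers who would answer remotely. Results are therefore in SD units, and that share is varied from 0 to 100%. (The Abstract speaks of enrolling 30. That discrepancy is a separate matter; the Statistical Analysis figures are used here.)

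**1. The plan's own figure.** The implied loss is 1 − 30/40 = 25%, and 30 / (1 − 0.25) = 40. The figures are consistent with each other. Because no rate is stated, 40 cannot be checked independently. The allowance is 10 people, or 5 per group if the loss is even.

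**2. Which outcomes a missed visit removes.**

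| Outcome | Captured at | Lost if time1 or time2 is missed? | Recoverable remotely? |
|---|---|---|---|
| Walk tests, chair rise, inspiratory pressure | onsite visit | yes, for that time point | no |
| mMRC, IPAQ, PROMIS Global Health, CAT | onsite visit | yes, for that time point | yes |
| Session attendance | weekly session | no | not needed |
| Activity log; visits, falls, injuries during the program | participant log and reports | no | not needed |

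For events after the last weekly session, the only contact described before time2 is a reminder email in the week of the assessment.

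**3. Standard error.** With the SD fixed and groups balanced, the SE is proportional to 1/√n.

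- Half of the 10 answer: n = 30 + 5 = 35; √(30/35) = 0.926, so the SE is about 7% lower.
- All 10 answer: n = 40; √(30/40) = 0.866, so the SE is about 13% lower.

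**4. 95% CI half-width for a between-group difference, in SD units:** t(0.975, n − 2) × √(1/n₁ + 1/n₂).

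- None answer, 15 v 15: 2.048 × √(2/15) = 0.748
- Half answer, 35 in total (18 v 17): 2.035 × √(1/18 + 1/17) = 0.688
- All answer, 20 v 20: 2.024 × √(2/20) = 0.640

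The largest gain is (0.748 − 0.640)/0.748 ≈ 14%; the smallest is zero. Performance tests gain nothing.

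**5. Uneven loss.** If 30 complete but split 20 v 10, the half-width is 2.048 × √(1/20 + 1/10) = 0.793 SD. That is slightly worse than 0.748, before any bias.

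**The case against.** **The article is condensed, and silence is not prohibition.** It does not say that questionnaires may be taken only in person, and a full protocol may have a missed-visit procedure. This stands as a limit: if such a route exists, it need only be stated. But the mode itself is positively stated twice, as in person and as onsite, and followed literally it loses the data.

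**It is tempting to say that a missed visit loses every outcome.** It does not. Attendance, the log and events during the program are collected elsewhere, and earlier time points are kept.

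**A reader might infer that tele-rehab participants will miss more visits, biasing the comparison.** The article does not support that. Everyone has completed onsite rehabilitation before and attends baseline onsite; parking is free, reminders are sent, and a gift card follows completion. At time2 neither arm has sessions. Dropout after learning the allocation could equally fall on the onsite arm, which must travel weekly. An illustration shows how far the answer depends on what is assumed. If 7 of 20 tele-rehab and 3 of 20 onsite participants are missing, and those missing score 0.5 SD worse than completers, the bias is (0.35 − 0.15) × 0.5 = 0.10 SD. Swap the counts and the sign reverses; make them 5 and 5 and it vanishes.

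**Nor is intention to treat contradicted.** Mode of collection does not conflict with it; it only limits the data available to carry it out.

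**REDCap is documented for consent only, and self-completion is not stated.** Both are correct. A remote form would be a new use of an available tool, and the present text has the blinded assessor conduct every assessment.

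**Dropouts may answer nothing, and remote answers may differ by mode.** Both are fair. The first is why the range starts at zero. The second is a real cost: with few remote respondents, possibly uneven by arm, a mode effect could not be adjusted for reliably.

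**Conclusion.** The point holds in limited form. The article ties four patient-reported outcomes to onsite visits without describing an alternative, so a missed time1 or time2 visit loses questionnaire data that need no site equipment. No figure in the plan is wrong and no two statements conflict; the stated method is weaker than an easily available one.

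The size depends on how many of the 10 allowed non-completers would answer. Across 0 to 100%, questionnaire n runs from 30 to 40 and the half-width from 0.75 to 0.64 SD. At half it is 0.69 SD, with the SE about 7% lower. These figures assume balanced groups and that all 10 miss the visit in question. Bias from arm-related missingness is possible, but the article supports neither a direction nor a size, so it should not be counted in the estimate. The gain is modest, but the change is worth making because it is cheap and serves the trial's estimation objective.

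**What to change.** Amend Outcome Assessments as follows.

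- Keep performance tests onsite and in-person assessment as the default for everything else.
- For participants who cannot attend time1 or time2, or who stop sessions but have not withdrawn consent, collect the mMRC, IPAQ, PROMIS Global Health and CAT within the same visit window, by REDCap link or by telephone from the blinded assessor.
- At the same contact, ask the event questions for the period since the last session.
- Record the mode for every response, report remote counts by arm, and add a sensitivity analysis restricted to in-person responses.

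**Cost.** Four short forms and a protocol amendment. Internet access, verified by email, is an inclusion criterion, and REDCap, email and telephone contact are already in use. With 11 participants enrolled at the time of writing, some would have been followed under the current rule; that should be reported. The remaining downside is a possible mode difference in a few responses, perhaps uneven by arm. The sensitivity analysis would show its influence but could not remove it.
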